### Clinical outcome measures

The FACIT-fatigue questionnaire has been validated in a mixed population of patients with IDA. The questionnaire consists of 13 items regarding fatigue. Each item has a response scale of 0–4, 0 being ‘not at all’ and 4 being ‘very much so’. The score for each item is added up to a summed score, where a low score equals more fatigue and higher score equals a better condition. Selected items are there for reversed when adding up the total score.

The Short Form 12 (SF-12) is used to evaluate quality of life (QoL). The SF-12 is derived from the more comprehensive SF-36. Both SF-12 and SF-36 cover the two summary measures of physical and mental health through eight domains/scales (physical functioning, physical role, bodily pain, general health, vitality, social function, emotional role, mental health) which in turn are covered by 12 items. Higher scores indicate better conditions.

RLS is evaluated by using the four diagnostic criteria [43] as a quantitative outcome which is either present or not present.

### Participant timeline {13}

The participants will attend the baseline visit and 4 follow-up visits: *T*_3w_ 3 weeks (± 2 days), *T*_6w_ 6 weeks (± 3 days), *T*_12w_ 12 weeks (± 1 week), and *T*_18w_ 18 weeks (± 1 week) from baseline (see Figs. 1 and 2).

**Fig. 1 Fig1:**
[figure not shown]
Illustration of trial flow (SF-12, Short Form 12; FACIT-fatigue, questionnaire on fatigue; AEs, adverse events; IDA, iron deficiency anaemia)

**Fig. 2 Fig2:**
[figure not shown]
Schedule for enrolment, intervention, and assessment during the trial

### Sample size {14}

The sample size calculations are based on the primary endpoint: Hb ≥ 11 g/dL (≥ 6.8 mmol/L) at all time points after baseline [1, 5]. The primary endpoint will be estimated by a Kaplan-Meier curve. Participants who drop out during the trial will be accounted for (set as ‘censored’) by the methodology and therefore not addressed specifically in the sample size calculations. It is assumed that 5% and 17.5% of the participants in the FDI and oral treatment groups respectively will have a Hb < 11 g/dL at some point during the trial, corresponding to 95% and 82.5% will have a Hb ≥ 11 g/dL at all post-baseline visits. Using a significance level of 5%, and setting the power to 80%, 100 participants in each treatment group are required in order to detect the assumed difference between FDI and oral iron.

### Recruitment {15}

The women will be recruited from the clinical setting. Standard clinical procedures for pregnant women at the trial site include 1st trimester screening for iron deficiency and anaemia by measuring Hb and serum ferritin. Women with ID or IDA are recommended intensified oral iron supplementation and repeated blood samples in the 2nd trimester. Women with persistent iron deficiency despite this standard oral treatment are contacted, informed about the trial, and are invited to the baseline visit.

## Assignment of interventions: allocation

### Sequence generation {16a}

The procedure for preparing the randomisation list is approved by the Global Trial Responsible Statistician. The randomisation list is prepared by BioStata ApS, Birkeroed, Denmark.

### Concealment mechanism {16b}

The allocation list is imputed in the electronic Case Report File (eCRF) and lies prepared within the eCRF. The sequence list is not accessible to the investigators.

### Implementation {16c}

The investigators consecutively invited all eligible participants to attend the baseline visit. At the baseline visit, demographics and latest Hb level are entered in the eCRF prior to randomisation. Thereafter, the participant is randomised stratified by Hb value and proceeds to the allocated treatment.

## Assignment of interventions: blinding

### Who will be blinded {17a}

This trial is open label. Neither the outcome assessors nor data analysts are blinded.

### Procedure for unblinding if needed {17b}

The design is open label so unblinding will not occur.

## Data collection and management

### Plans for assessment and collection of outcomes {18a}

Data is collected during the five trial visits and by medical record follow-up. Source data is defined as all information in original records or certified copies of original records of clinical findings, observations, or other activities in a clinical trial necessary for reconstruction and evaluation of the trial. Source data is entered from paper source into an eCRF.

Laboratory analysis data is drawn electronically from the hospitals IT system to the eCRF.

### Plans to promote participant retention and complete follow-up {18b}

The participant has the right to withdraw from the trial at any time and for any reason without prejudice to her future medical care by the physician or at the institution. If a participant withdraws from the trial, the investigator will perform all final visit assessments besides the scheduled trial assessments for that visit.

As part of the subject information, the purpose of the trial and the importance of completing the trial will be explained to the subjects. Subject compliance (oral iron group) will be followed throughout the trial and advices and guidelines provided in case of non-compliance. Both treatment groups will be in regular contact with the investigator.

In extraordinary/force major situations, the principal investigator can temporarily suspend trial visits, e.g. if entering the hospital carries a risk for the participant. In such case, we will attempt to collect information via telephone or email, where possible, and schedule trial-related laboratory analyses simultaneously with any pre-scheduled appointments in a clinical setting. The authorities will be informed promptly in case of such temporary restructuring actions, including the reason for the decision.

### Data management {19}

Data management is outsourced. The data collection tool for this trial is the eCRF, which is compliant with 21 CFR Part 11 regulations. Clinical data management is performed in accordance with applicable standards and data cleaning procedures.

### Confidentiality {27}

Data are handled confidentially and stored in a locked archive.

### Plans for collection, laboratory evaluation, and storage of biological specimens for genetic or molecular analysis in this trial/future use {33}

Blood samples will be collected by venous puncture at every participant visit. Haematological indices of ID/IDA as well as safety indices will be analysed within hours and evaluated by the investigators during the next working day at the latest. A single tube containing plasma from each visit will be stored at the trial site and will be used to assess hepcidin at an external laboratory. The samples will be destroyed after analysis or latest at completion of the trial. Thus, specimens collected at trial visits will not be used for genetic analyses or analyses in any future trials.

## Statistical methods

### Statistical methods for primary and secondary outcomes {20a}

Time to Hb < 11 g/dL and proportion of participants with correction of anaemia (Hb ≥ 11.0 g/dL) at *T*_3w_, *T*_6w_, and *T*_12w_ will be estimated by a Kaplan-Meier curve using scheduled visits. Based on the Kaplan-Meier curve, the proportion of participants who have met the primary endpoint (achievement/maintenance of Hb ≥ 11 g/dL at all post-baseline visits) at *T*_18w_ will be estimated and compared between the treatment groups.

The primary endpoint analysis will be performed for the intention-to-treat analysis set and will be repeated for the full analysis set and per protocol analysis sets.

As sensitivity, the risk difference will be used to compare the proportion of participants with Hb ≥ 11 g/dL at all post-baseline visits. Risk difference and the associated 95% Newcombe CI and *p* value will be calculated, adjusting for strata (Hb </≥ 11 g/dL at inclusion) using the Cochran-Mantel-Haenszel method. In this analysis, participants who do not complete the study period will be set as failures.

The change in Hb and biochemical safety parameters from baseline to *T*_3w_, *T*_6w_, *T*_12w_, and *T*_18w_ will be analysed using a restricted maximum likelihood-based mixed model for repeated measures approach.

The proportion of participants who (a) receive an additional IV FDI dose, (b) receive allogenic RBC transfusions, (c) discontinue from the trial because of lack of response or intolerance of investigational drugs, and (d) develop hypophosphatemia will be compared between the treatment groups by Fisher’s exact test.

The number of units of RBC transfused per transfused participant from baseline to final subject visit will be compared between the treatment groups by an analysis of variance or Wilcoxon test.

For participants in the oral iron group, AEs with onset at/after the time of first additional IV iron isomaltoside dose will be excluded from the main AE summaries. In addition, displays of all AEs per overall treatment group will be produced, as well as summaries and participant listings of AEs occurring at/after the time of first additional IV iron isomaltoside dose.

Medical record follow-up will be tabulated by descriptive statistics.

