### Trial design {8}

The trial is a randomised, comparative, open-label, single-centre, phase IV trial, with planned 200 women randomised 1:1 to a single dose of IV FDI or a fixed dose of oral iron ferrous fumarate with ascorbic acid. The randomisation is stratified by Hb value (≥ or < 11.0 g/dL).

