### Outcomes {12}

The primary endpoint of this trial is a Hb ≥11.0 g/dL (≥ 6.8 mmol/L) at all trial visits post-baseline (*T*_3w_, *T*_6w_, *T*_12w_, and *T*_18w)._

The secondary endpoints are Hb ≥ 11.0 g/dL (≥ 6.8 mmol/L) at each follow-up visit, change in Hb and other haematological indices of ID/IDA from baseline to each follow-up visit (e.g. reticulocytes, reticulocyte haemoglobin content (CHr), *s*-ferritin, *s*-transferrin, *s*-iron, hepcidin, and calculated transferrin saturation (TSAT)), incidence of hypophosphatemia (defined as serum [*s*]*-*phosphate < 2 mg/dL) from baseline to each follow-up visit, change in fatigue and quality of life questionnaires from baseline to each follow-up visit, presence of RLS at each follow-up visit, number of participants who receive an additional IV iron isomaltoside dose at *T*_6w_ and/or *T*_12w_, reason for the additional IV iron isomaltoside dose (non-compliance, lack of effect), number of participants receiving RBC transfusions and the number of RBC units per transfused participant from baseline to final subject visit, type and incidence of AEs observed at any time until final subject visit, serious or severe hypersensitivity reaction starting at or after the first dose of randomised treatment, AEs of special interest (constipation, diarrhoea, flatulence, nausea, vomiting, abdominal pain, dyspepsia, dysgeusia, and stool discoloration), number of participants who discontinue from the trial because of lack of response or intolerance of investigational drugs, foetal bradycardia related to infusion of IV iron isomaltoside at or after GA 26, change in biochemical safety parameters from baseline to each follow-up visit, and compliance to treatment: at baseline in the IV group and at *T*_6w_ and *T*_18w_ in the oral group.

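### The share of women with Hb at or above 11 g/dL at T6w and T12w is to be read from a Kaplan-Meier curve of time to Hb below 11, which cannot show recovery

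*Protocol article*

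**What the plan says.** The Outcomes section {12} separates two endpoints. The primary is Hb ≥ 11.0 g/dL at every post-baseline visit (T3w, T6w, T12w and T18w). The list of secondary endpoints opens with the same threshold taken "at each follow-up visit, change in Hb and other haematological indices of ID/IDA from baseline to each follow-up visit". Its first item is therefore threshold status at a visit, and the change in Hb is a separate item.

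The section on statistical methods for primary and secondary outcomes {20a} then names two quantities in one sentence: time to Hb < 11 g/dL, and the "proportion of participants with correction of anaemia", glossed as Hb ≥ 11.0 g/dL, at T3w, T6w and T12w. Both "will be estimated by a Kaplan-Meier curve using scheduled visits". The next sentence takes the primary endpoint at T18w from the same curve. The stratified risk difference in that section is specified only for the all-visits endpoint, and the mixed model is for change from baseline.

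Two other sections bear on recovery. Under Trial design {8}, randomisation is stratified by Hb below or at least 11.0 g/dL, so women already below 11 can enter. Section {11b} allows an additional IV dose in either group for iron deficiency anaemia at T6w or T12w.

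**The concern.** A Kaplan-Meier curve of time to first Hb < 11 can only fall. A woman below 11 at T3w who is at or above 11 at T6w and T12w is an event at T3w and stays one. No correction after T3w can appear on the curve, although correction is what the sentence says is being estimated.

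The method as stated therefore gives a different quantity from the endpoint as stated. If it is followed, the T6w and T12w proportions will be reported under the wrong name and will be too low wherever women recover. The gap need not be equal in the two arms, so the treatment comparison at those visits can shift as well.

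**Working it through.** **1. The plan's own figure.** The planning inputs are: "It is assumed that 5% and 17.5% of the participants in the FDI and oral treatment groups respectively will have a Hb < 11 g/dL", "corresponding to 95% and 82.5% will have a Hb ≥ 11 g/dL at all post-baseline visits", a 5% significance level, and "setting the power to 80%, 100 participants in each treatment group are required" (Sample size {14}), "with planned 200 women randomised 1:1" (Trial design {8}). The two-sided pooled two-proportion formula, with mean proportion (0.95 + 0.825)/2 = 0.8875, gives

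n = [1.960·√(2 × 0.8875 × 0.1125) + 0.842·√(0.95 × 0.05 + 0.825 × 0.175)]² / 0.125² = 99.1, rounded up to 100 per group.

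Power at 100 per group is 80.3%. The figure reproduces, and it concerns the all-visits endpoint only.

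**2. The two quantities.** Let S(t) be the probability of Hb ≥ 11 at every visit up to t, which the curve estimates. Let P(t) be the probability of Hb ≥ 11 at visit t, which is the secondary endpoint. Every woman counted in S(t) is also counted in P(t), so S(t) ≤ P(t). The gap is the share with an earlier value below 11 who are at or above 11 at t. T3w is the first post-baseline visit, so the gap there is zero, missing data aside.

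**3. Size, as an illustration.** The protocol supplies S(T18w) = 82.5% (oral) and 95% (FDI). The following are assumed:
- all women start at or above 11, with no dropout;
- the chance f of falling below 11 is the same at each of the four visits;
- a woman below 11 has chance r of being at or above 11 at the next visit, with r the same in both arms.

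The protocol does not give r, so a range is shown.

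- f = 1 − 0.825^(1/4) = 0.0470 (oral) and 1 − 0.95^(1/4) = 0.0127 (FDI).
- S at visit k is (1 − f)^k, with T12w as k = 3.
- P at the first visit is 1 − f; after that, P(next) = P·(1 − f) + (1 − P)·r.

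Oral arm at r = 0.5:
- T6w: 0.9530 × 0.9530 + 0.0470 × 0.5 = 0.932
- T12w: 0.9318 × 0.9530 + 0.0682 × 0.5 = 0.922
- Curve at T12w: 0.9530³ = 0.866

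| Visit, arm | Curve | P, r = 0.25 | P, r = 0.5 | P, r = 0.75 |
|---|---|---|---|---|
| T3w, oral | 95.3% | 95.3% | 95.3% | 95.3% |
| T3w, FDI | 98.7% | 98.7% | 98.7% | 98.7% |
| T6w, oral | 90.8% | 92.0% | 93.2% | 94.4% |
| T6w, FDI | 97.5% | 97.8% | 98.1% | 98.4% |
| T12w, oral | 86.6% | 89.7% | 92.2% | 94.2% |
| T12w, FDI | 96.2% | 97.1% | 97.8% | 98.4% |

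At T12w the curve is about 3 to 8 points too low in the oral arm and about 1 to 2 points too low in the FDI arm. With r = 0 there is no gap.

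**4. Effect on the comparison.** The T12w difference between arms is 9.7 points on the curve (from unrounded values). Visit by visit it is 97.1 − 89.7 = 7.4 points at r = 0.25, 97.8 − 92.2 = 5.6 at r = 0.5 and 98.4 − 94.2 = 4.2 at r = 0.75. The direction depends on r. If no oral-arm woman recovered and r were 0.75 in the FDI arm, the difference would be 98.4 − 86.6 = 11.8 points, larger than on the curve.

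**The case against.** The strongest reply is that this is a wording slip in one secondary endpoint. The curve is a proper estimator of the primary endpoint, and change in Hb at all four visits has its own mixed model. That stands, and it limits the weight of the point. It does not remove the point, because the section names a method that cannot give the named quantity. This is not a detail left to an unseen analysis plan.

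A second reply is that a separate curve of time to correction was meant. None is described, and such a curve would give cumulative first correction, not status at a visit. It can also be said that the protocol never expressly equates correction of anaemia with the secondary endpoint. That is true, but the gloss Hb ≥ 11.0 g/dL is the same threshold, and on either meaning correction after T3w is invisible on the curve.

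A third reply is that a per-visit proportion has its own difficulty. Additional IV iron at T6w or T12w follows the woman's event and so leaves the curve untouched, whereas a later per-visit proportion would include her recovery. That stands, and the fix has to deal with it.

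Stronger readings are tempting, but the protocol does not support them:
- **All three visits are biased.** A reader might infer this, but T3w is not affected.
- **T18w lacks an analysis.** The section uses the curve at T18w only for the primary endpoint. A condensed article may leave the secondary analysis at that visit to the analysis plan.
- **The error is half the planned effect.** If 10% of an arm began below 11, 80% of these were still below at T3w and 80% of those had recovered by T12w, the gap would be 0.10 × 0.80 × 0.80 = 6.4 points, about half of 12.5. Nothing in the protocol supports the 10%, and the Discussion calls iron deficiency anaemia rare at that stage. The gap also exceeds the 5% of FDI women assumed ever to fall below 11. Finally, an error within one arm cannot be set against a between-arm difference in another endpoint.

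**Conclusion.** The point holds for T6w and T12w. The stated method estimates the share never below 11 so far and understates the share at or above 11 at the visit whenever women recover. That direction within each arm follows from the definitions, missing data aside. The sizes rest on the planning proportions, a constant per-visit risk, no dropout and an assumed recovery chance, so they are an illustration and not a forecast. The shift in the between-arm difference, from 9.7 to 5.6 points at T12w, also needs a recovery chance of 0.5 in both arms.

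A reader might infer that the primary result or the 100 per group is in doubt. Neither is. The matter should be fixed, but it carries the weight of a secondary endpoint.

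**What to change.** - Keep the Kaplan-Meier curve for time to first post-baseline Hb < 11 and for the all-visits primary endpoint.
- Analyse Hb ≥ 11 at each follow-up visit as a binary outcome, using the Cochran-Mantel-Haenszel risk difference with Newcombe interval already named in {20a}, stratified by baseline Hb.
- Report correction of anaemia as that proportion within the baseline Hb < 11 stratum. This group may be small, so simple description may be all it can bear.
- State how a missed visit is counted, and whether the rule that non-completers are failures carries over from the sensitivity analysis.
- State how Hb values after an additional IV iron dose are counted, and show how many women at each visit this concerns.

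Hb is already measured at every visit, so no new data are needed. The cost is a few sentences and one table. The downside is that proportions after T6w may include women given additional IV iron, which the stated rule must make explicit. Because the trial is open label and the analysts are not blinded {17a}, the wording should be settled before the analysis.

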## Introduction

### Background and rationale {6a}

Untreated iron deficiency (ID) in pregnancy can lead to iron deficiency anaemia (IDA) [1, 2]. ID in pregnancy is defined by low iron stores, measured by a level of circulating ferritin < 30 μg/L [3–6]. Iron is essential for basic cellular processes, such as cell division and the synthesis of haemoglobin (Hb) [7]. Anaemia in pregnancy is defined by a Hb level < 11.0 g/dL, WHO [1, 5]. Thus, IDA in pregnancy is defined as Hb < 11.0 g/dL and serum-(*s*)-ferritin < 30 g/μg/L.

In Danish pregnant women, who do not take iron supplementation, approximately 50% have ID and 21% have IDA [8]. Anaemia (regardless the cause) is estimated to occur in 24% of Danish pregnant women (WHO).

The prevalence of ID is approximately 7% in 1st trimester, 14–40% in 2nd trimester, and 30–62% in 3rd trimester [9, 10]. Prevalence of IDA is approximately 2% in 1st trimester, 8% in 2nd trimester and, 27% in 3rd trimester [11, 12]. The steep increase in ID and IDA through the trimesters illustrates that women with ID in the beginning of pregnancy have a great risk of developing IDA during pregnancy.

National recommendations on routine iron supplementation in pregnancy do not necessarily prevent ID and IDA as seen in a Swizz study, where approximately 32% of pregnant women in 2nd trimester had ID and 6.2% IDA despite a recommended daily oral iron dose of 80 mg [13].

Maternal symptoms of ID and IDA include fatigue/exhaustion, reduced physical performance, restless legs syndrome (RLS), and decreased ability to cope with blood loss during delivery. Severe anaemia may cause dizziness, shortness of breath, palpitation, orthostatism, and syncope [14, 15]. Iron is an essential part of myoglobin, which explains why ID may compromise contractility in the uterine musculature that in turn may increase the risk for prolonged labour, caesarean section, and postpartum haemorrhage [16, 17]. The consequence of maternal anaemia for the foetus is low birthweight, which can complicate the neonatal period [18–21]. ID during foetal life may adversely affect brain development with long-term deficits. One trial showed that maternal anaemia in pregnancy could be linked to 14% of cases of mental retardation at a 7-year follow-up [22].

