### Objectives {7}

In order to prevent IDA throughout the trial in pregnant women, who have ID after 4 weeks of standard treatment, the primary objective is to compare the efficacy of a single dose of IV administered FDI with a fixed dose of oral ferrous fumarate containing ascorbic acid.

The secondary objectives are to compare the effect of IV FDI and oral ferrous fumarate with ascorbic acid on (i) haematological indices of IDA in maternal blood, (ii) maternal fatigue and quality of life (QoL), (iii) RLS, (iv) the need for an additional IV FDI dose or (rescue) red blood cell (RBC) transfusion, and (v) safety.

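### The primary Kaplan-Meier comparison pools women already anaemic at baseline with women at risk of anaemia, states no stratum adjustment, and leaves no planned estimate of prevention alone

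*Protocol article*

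**What the plan says.** All references are to the protocol article.

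- **Objectives {7}** frame the aim as prevention: "In order to prevent IDA throughout the trial in pregnant women". The Discussion says the design was changed from treating established anaemia to preventing it.
- **Eligibility criteria {10}** select on ferritin. Hb excludes a woman only at transfusion level, so a woman below 11 g/dL can enter.
- **Trial design {8}** provides for such women: "The randomisation is stratified by Hb value (≥ or < 11.0 g/dL").
- **Outcomes {12}**: "The primary endpoint of this trial is a Hb ≥11.0 g/dL" at all four post-baseline visits, the first at 3 weeks.
- **Statistical methods {20a}** describe the endpoint as "achievement/maintenance of Hb ≥ 11 g/dL at all post-baseline visits". Time to Hb below 11 g/dL is estimated by Kaplan-Meier, then "Based on the Kaplan-Meier curve, the proportion of participants who have met the primary endpoint" at T18w is compared between groups in the intention-to-treat set. No test, weighting or stratum is named for this comparison. The sensitivity risk difference is adjusted for the Hb stratum by Cochran-Mantel-Haenszel, with non-completers counted as failures.
- **Additional analyses {20b}**: none is planned.
- **Sample size {14}**: "It is assumed that 5% and 17.5% of the participants in the FDI and oral treatment groups respectively" will fall below 11 g/dL at some point, which gives 100 per group for 80% power at the 5% level. The rates are not split by baseline Hb.

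**The concern.** A woman with baseline Hb below 11 g/dL is already in the event state when the time-to-event clock starts. Anaemia cannot be prevented in her. She can succeed only if her Hb is corrected by the 3-week visit and then held. A woman at or above 11 g/dL succeeds by never falling below. One curve over both groups answers two questions at once, while the trial's conclusion will be read as an answer to the prevention question.

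Baseline Hb relative to 11 g/dL is also likely to be a strong predictor of the outcome. An unadjusted comparison of proportions then carries between-stratum variation that the randomisation stratum could remove. The adjusted sensitivity analysis does not fill the gap: it still yields one pooled figure, and it changes the handling of non-completers as well, so it is not a stratified version of the primary analysis.

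**Working it through.** **Step 1. Reproduce the plan's figure.** Inputs from Sample size {14}: p₁ = 0.05, p₂ = 0.175, alpha 5% (taken as two-sided), power 80%. With the mean rate 0.1125:

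n = [1.960·√(2 × 0.1125 × 0.8875) + 0.842·√(0.0475 + 0.1444)]² / 0.125² = (0.876 + 0.369)² / 0.0156 ≈ 99.1, so 100 per group.

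Power at 100 per group is 80.3% (pooled variance) or 81.4% (unpooled). The stated size reproduces.

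**Step 2. What the article says about the anaemic share.** It gives no figure for the enrolled women. The Discussion calls iron deficiency anaemia rare at this stage in Danish women. Background {6a} puts it at about 8% of pregnant women in the 2nd trimester, and cites a Swiss study "where approximately 32% of pregnant women in 2nd trimester had ID and 6.2% IDA". That is 6.2/32 = 19% of iron-deficient women if the 32% includes the anaemic women, or 6.2/38.2 = 16% if it does not. I use 5%, 10% and 20%, all as assumptions.

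**Step 3. Reading A: 5% and 17.5% describe only women with Hb ≥ 11 g/dL.** Let x be the anaemic share and q₁, q₂ the failure rates of anaemic women on FDI and oral iron (assumed). Censoring is ignored, as it is in the sample size calculation.

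- Overall rate in an arm: P = (1 − x)·p + x·q
- Unstratified power: Φ(d / √[(P₁(1 − P₁) + P₂(1 − P₂))/100] − 1.96), with d = P₂ − P₁
- Stratified power: the same d, with variance [(1 − x)·V₀ + x·V₁]/100, where V₀ = 0.0475 + 0.1444 = 0.1919 and V₁ = q₁(1 − q₁) + q₂(1 − q₂)

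Example, x = 10% and q = 80% in both arms: P₁ = 0.045 + 0.08 = 0.125; P₂ = 0.1575 + 0.08 = 0.2375; d = 0.1125.

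- Unstratified: standard error √(0.2905/100) = 0.0539; Φ(2.087 − 1.96) = 55%.
- Stratified: variance (0.9 × 0.1919 + 0.1 × 0.32)/100 = 0.002047, standard error 0.0452; Φ(2.487 − 1.96) = 70%.

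| x | q₁ v q₂ | P₁ v P₂ | Difference (points) | Unstratified | Stratified |
|---|---|---|---|---|---|
| 5% | 80% v 80% | 8.75% v 20.6% | 11.9 | 67% | 76% |
| 10% | 80% v 80% | 12.5% v 23.75% | 11.25 | 55% | 70% |
| 20% | 80% v 80% | 20% v 30% | 10.0 | 38% | 57% |
| 10% | 70% v 90% | 11.5% v 24.75% | 13.25 | 69.5% | 84% |

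With failures of 50% v 90% at x = 8%, the difference is 14.7 points. Power is then 82% crude and 91% with a Cochran-Mantel-Haenszel test (simulated).

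The difference is d = (1 − x)·12.5 + x·(q₂ − q₁) in points. It falls below 12.5 only if the gap between arms among anaemic women is below 12.5 points.

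**Step 4. Reading B: the rates describe all participants.** Power stays at 80.3%. The rates do then constrain the mix. Even if no FDI woman with Hb ≥ 11 g/dL ever failed, the failure rate among anaemic FDI women could be at most 5%/x: 50% at x = 10%, and 26% at x = 19.4%. If all anaemic women failed, x could not exceed 5%.

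**Step 5. Prevention stratum alone.** At x = 10%, 90 women per arm remain. At 5% v 17.5%, power is about 76% (pooled variance) or 77% (unpooled).

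**The case against.** The strongest reply has four parts.

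1. **Silence on the stratum.** A reader might infer that the primary analysis ignores the stratum. The article does not say so. It names neither a stratified nor an unstratified test, and such detail may sit in the full protocol or SAP. This stands: the most that can be said is that adjustment is not stated for the primary comparison, although it is stated for the sensitivity analysis in the same section.
2. **Disclosed mixture.** The endpoint wording covers both achievement and maintenance, and a single intention-to-treat estimate over all randomised women is legitimate and unbiased between arms. This also stands, but that estimate still does not answer the prevention objective, and no planned analysis does so separately.
3. **Dilution.** A reader might infer that pooling dilutes the effect. The documents do not support that as a general claim. With anaemic women failing at 70% v 90%, the difference grows to 13.25 points.
4. **Power.** A reader might infer that the stated power is not delivered. That is not shown. The sample size reproduces, its rates are worded for all participants, and the loss appears only if they are reassigned to one stratum and combined with an assumed share and assumed failure rates. If anaemia is as rare at enrolment as the Discussion says, the larger losses are unlikely.

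**Conclusion.** The point holds as a mismatch between objective and analysis, with a likely loss of precision. It is not an error in the sample size and not a source of bias. Three facts rest on the text alone: anaemic women can be randomised, they start in the event state of the primary curve, and no planned analysis separates prevention from correction.

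The effect on power is conditional. Under Reading A with 10% anaemic, it is about 55% unstratified v 70% stratified at 80% failure in both arms, and about 70% v 84% at 70% v 90%. Under the literal wording of the sample size section it stays about 80%. The anaemic share and all failure rates among anaemic women are assumptions. In every scenario in the table, the stratified comparison has more power than the unstratified one.

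**What to change.** 1. Make the primary comparison a stratum-weighted difference in Kaplan-Meier proportions at T18w, using the randomisation stratum (Hb < or ≥ 11 g/dL) that the sensitivity analysis already uses.
2. Pre-specify the Hb ≥ 11 g/dL stratum estimate as the one that supports any claim of prevention, and report the Hb < 11 g/dL stratum separately as correction.
3. As a minor clarification, state whether the 5% and 17.5% planning rates include women with baseline Hb below 11 g/dL.

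The cost is wording in the article and SAP. The stratum is recorded before randomisation, so no new data are needed. Recruitment has closed (Trial status), so the analysis is what can still change. Because the trial is open-label and analysts are not blinded ({17a}), these choices need to be fixed before the outcome data are analysed. The downside is that the prevention estimate rests on fewer than 200 women, with somewhat lower power than the full set was planned to have (Step 5).
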